#### **12.1.2 Expedited Adverse Event Reporting**

##### Expedited Adverse Event Reporting to DAIDS

Requirements, definitions and methods for expedited reporting of Adverse Events (AEs) are outlined in Version 2.0 of the DAIDS EAE Manual, dated January 2010, which is available on the RSC website (<http://rsc.tech-res.com/safetyandpharmacovigilance/>). The DAIDS Adverse Experience Reporting System (DAERS), an internet-based reporting system, must be used for expedited AE reporting to DAIDS. In the event of system outages or technical difficulties, expedited AEs may be submitted via the DAIDS EAE Form.

The current DAIDS EAE Manual (Version 2.0), which is also available on the RSC website at: <http://rsc.tech-res.com/safetyandpharmacovigilance/>. The DAIDS Adverse Experience Reporting System (DAERS), an internet-based reporting system, will be used for expedited AE reporting to DAIDS. In the event of system outages or technical difficulties, expedited AEs will be submitted via the DAIDS EAE Form. This form is available on the RSC website: <http://rsc.tech-res.com/safetyandpharmacovigilance/>.

##### Reporting Requirements for this Study

The SAE Reporting Category, as defined in Version 2.0 of the DAIDS EAE Manual, will be used for this study. The study agents that must be considered in determining relationships of AEs requiring expedited reporting to DAIDS are: MB66 film, and placebo film.

##### Reporting Period

AEs must be reported on an expedited basis during the entire study duration for an individual subject (from study enrollment until study completion or discontinuation of the subject from

study participation for any reason). After the protocol-defined AE reporting period, unless otherwise noted, only Suspected, Unexpected Serious Adverse Reactions (SUSARs) as defined in Version 2.0 of the EAE Manual will be reported to DAIDS if the study staff become aware of the events on a passive basis (from publicly available information).

## **13. CLINICAL MANAGEMENT**

### **13.1 CLINICAL MANAGEMENT OF ADVERSE EVENTS**

By definition, an adverse event can be either a new finding or symptom or a worsening of a pre-existing condition. In order to accurately capture adverse events in follow-up, a thorough baseline history will be obtained at Visit 1 and Visit 2. For example, for participants who endorse a history of headache, site staff will probe for and record details surrounding the condition such as frequency, location, duration, medication use, triggers, etc. Only by eliciting a full description will study staff be equipped to determine whether a subsequent event in follow-up is a clinically distinct event. Adverse events will be elicited during the safety contact telephone call and in-clinic follow-up visits. Referral to appropriate care will be offered to participants as needed. Vaginally applied medications as management for AEs should be avoided if possible (instead using systemic medication for treatment where appropriate). Criteria for product hold for AEs thought related to the study film, and for discontinuation of an individual's participation in the study are described below.

### **13.2 PREGNANCY**

Pregnancy during study participation is unlikely due to the requirement for effective contraception. However, urine pregnancy tests will be performed during the investigational protocol. Participants who become pregnant in follow-up will be referred for obstetric care. The participant will be permanently discontinued and the following procedures will be performed at discontinuation: complete metabolic panel and complete blood count. Pelvic exams will only be performed to evaluate a participant's reported symptom. No genital specimens will be collected in a pregnant participant. Staff will continue follow-up contact with the participant to obtain pregnancy outcome data. Of note, the participant will be encouraged to continue in the study so that safety data might be collected. See further detail in Section [11.2.3](#).

### **13.3 ACQUISITION OF HIV INFECTION ON STUDY**

See Section [11.2.2](#).

### **13.4 UNEXPECTED MENSTRUAL LIKE BLEEDING**

In instances when unexpected menstrual like bleeding occurs, participants will be instructed to come to the study site for an evaluation. This unexpected bleeding will be considered an adverse event and appropriate clinical management will be based on exam findings.

Because every attempt will be made to enroll a participant into the study during the first two weeks of her menstrual cycle (Segment A) or first week of her menstrual cycle (Segment B), it is unlikely that a participant will menstruate during the period of product use. In the setting of menses or menses like bleeding that occurs during the week of product use, product use will be held and the PSRT consulted.

### **13.5 CRITERIA FOR DISCONTINUATION**

Participants may voluntarily withdraw from the study for any reason at any time. The Site PI/designee also may withdraw participants from the study to protect their safety and/or if they are unwilling or unable to comply with required study procedures. Participants also may be withdrawn if the study sponsors, government or regulatory authorities, including the Office of Human Research Protections (OHRP), or site IRBs/ECs terminate the study prior to its planned end date. Every reasonable effort will be made to complete a final evaluation of participants who withdraw or are withdrawn from the study prior to completing the follow-up Visit. Study staff members will record the reason(s) for all withdrawals in participants' study records.

### **13.6 PRODUCT HOLD**

Because of the short duration of both Segments of the study (single dose in Segment A, 7 daily doses in Segment B), product holds are not anticipated to be useful. Instead, participants with Grade 1 or 2 adverse events will be allowed to complete the exposure period for Segment B. For Grade 3 or 4 AEs, rather than product hold, product use will be discontinued permanently. In the unlikely event that a participant is intolerant of the study product immediately after placement, the site clinician will perform a pelvic exam and cervicovaginal lavage to remove all visible product.

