### **13.7 CRITERIA FOR DISCONTINUATION**

#### **13.7.1 Permanent Intervention Discontinuation,**

The criteria for permanent discontinuation of further study product(s)/ intervention(s) for an individual participant are:

- a) Grade 3 or 4 Adverse Event (per Section [13.6](#))
- b) Requirement for prohibited concomitant medications
- c) Pregnancy
- d) Completion of study product course as defined in the protocol
- e) Request by participant to terminate study product
- f) Clinical conditions, which in the best judgment of the investigator, are believed to be harmful or potentially life-threatening to the participant, even if not addressed in the AE Management section of the protocol
- g) Recommended by the EC/IRB, PSRT, DAIDS Medical Officer, OHRP, or FDA

The participant will continue to be followed with her permission if study product is discontinued. No subsequent modifications to the visit schedule and duration of continued follow-up will be made, except for discontinuation of the study product.

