## **13.8 SAFETY MONITORING**

The study site investigators are responsible for continuous close safety monitoring of all study participants, and for alerting the Protocol Team and IRB if unexpected concerns arise. A sub-group of the Protocol Team, including the Protocol Chair or designee, the DAIDS Medical Officer, and an IPCP Co-PI will serve as the Protocol Safety Review Team (PSRT). If necessary, external experts representing expertise in the fields of microbicides, biostatistics, HIV transmission, and medical ethics may be invited to review the events. The PSRT and the study site will cooperate closely to monitor participant safety and respond to occurrences of toxicity in a timely manner. Study staff will seek to maintain close and effective communication with study participants and communication with and cooperation among study staff, investigators, the PSRT, and the DAIDS Medical Officer. The following findings will serve as the minimum criteria to pause or stop enrollment in Segment A, prevent the initiation of Segment B, and pause or stop enrollment in Segment B. However DAIDS and/or the PSRT can stop the study at any time for any concerning findings of lesser severity than those listed here:

1. If any participant manifests a grade 3 or higher AE that is judged to be related to study product
2. If any participant develops deep epithelial disruption or ulceration of the genital epithelium.
3. If any participant develops erythema or edema of more than 50% of the combined vaginal and cervical surface (grade 2) or more than 50% of the vulvar surface (grade 2).

If enrollment is paused, its reinstitution will require the unanimous agreement of all members of the PSRT.

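### A genital finding that pauses enrollment under 13.8 does not automatically stop film for the woman who has it, because 13.6 and 13.7.1 stop dosing by grade only at Grade 3 or 4

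*Protocol*

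**What the plan says.** Five sections of the protocol bear on whether a woman in Segment B keeps inserting film after an adverse event.

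- **13.1** announces that "Criteria for product hold for AEs thought related to the study film", along with criteria for discontinuation, will follow.
- **13.4** covers menstrual-like bleeding. "This unexpected bleeding will be considered an adverse event", and for the dosing week the instruction reads "menses or menses like bleeding that occurs during the week of product use, product use will be held and the PSRT consulted". No grade threshold is set.
- **13.6**, headed Product Hold, expects holds to be of little use because exposure is short. Instead, "participants with Grade 1 or 2 adverse events will be allowed to complete the exposure period for Segment B", and Grade 3 or 4 events lead to permanent discontinuation of product.
- **13.7.1** lists the grounds for permanently stopping product. Item (a) is a Grade 3 or 4 event. Items (e) to (g) are the woman's request, "Clinical conditions, which in the best judgment of the investigator, are believed to be harmful or potentially life-threatening to the participant", and a recommendation from the PSRT or another oversight body.
- **13.8** gives the "minimum criteria to pause or stop enrollment in Segment A, prevent the initiation of Segment B, and pause or stop enrollment in Segment B". Criterion 2 reads "If any participant develops deep epithelial disruption or ulceration of the genital epithelium", with no grade attached. Criterion 3 is "erythema or edema of more than 50% of the combined vaginal and cervical surface (grade 2", closing bracket omitted here, or the same extent on the vulvar surface, also labelled grade 2.

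**The concern.** Section 13.8 acts on enrollment and on the start of Segment B. It does not address dosing in the woman whose finding triggered it. Her dosing is governed by 13.6 and 13.7.1, which sort events by grade and draw the line at Grade 3. Criterion 3 is grade 2 on the protocol's own label, so it falls on the side that may continue. Criterion 2 has no grade, so a stop is assured only if it happens to be graded 3 or higher.

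This is first-in-human use. In the rabbit study in 6.1.3, dry film at about five times the human mg/kg dose gave bleeding in 3 of 9 animals, with ulcers, inflammation and thrombi. The protocol gives good reasons why this may not carry over: the film was tightly wound, the exposed epithelium was not keratinized, solubilized film gave no significant findings, and macaques on dry half-film had no adverse events. The human risk may be small. Even so, lesions of this kind are what 13.8 guards against, and a finding grave enough to halt entry of new women should by default halt further exposure of the woman who has it.

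**Working it through.** **Step 1. Follow one finding through the sections.** Take erythema of more than half of the combined vaginal and cervical surface.

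| Section | Consequence |
|---|---|
| 13.8, criterion 3 | Enrollment pauses or stops; her own film is not mentioned |
| 13.6 | Grade 2, so she may complete dosing |
| 13.7.1(a) | Not met; needs Grade 3 or 4 |
| 13.7.1(e)-(g), 13.5, 13.7.2(e) | She can be stopped, by her request or by judgment |

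Nothing in the finding itself stops the film. For criterion 2 the result is the same unless the lesion is graded 3 or higher.

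**Step 2. Can it arise while doses remain?** Yes. Visit 3 (Day 1) includes a speculum exam and is also the visit at which 8 films are dispensed for home use (Table 12). Dosing is one film a day on Days 0 to 6, or Days 0 to 7 if Visit 4 falls on Day 8 (10.3).

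- Visit 4 on Day 7: films after the Day 1 exam = Days 1 to 6 = 6 of 7; 6/7 = 86%.
- Visit 4 on Day 8: Days 1 to 7 = 7 of 8.

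These are the most that the default permits, not a forecast. The next scheduled exam is Visit 4; the contact in between is the Day 3-4 telephone call.

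**Step 3. The bleeding hold.** Grade 1-2 menses-like bleeding in the dosing week is an adverse event under 13.4 and must be held. Under 13.6 the same event may continue. Neither section refers to the other.

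**Step 4. The pointer in 13.1.** The one hold in the sections that follow is the one in 13.4, which does not depend on relatedness. Section 13.6 gives a disposition by grade but no hold criteria for related events.

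**Step 5. Does stopping such a woman disturb the primary analysis?** A woman stopped before the dose on the day before Visit 4 fails the evaluability rule in 14.2 and is replaced, but her adverse event is kept in the primary analysis. With one such woman the arm has 16 rather than 15. The one-sided 95% Clopper-Pearson upper limit for x events in n is the p that solves P(X ≤ x | n, p) = 0.05.

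- Plan's own figure: 1/15 gives 27.9%, reproduced (27.94%). 2/15 gives 36.3%.
- One woman replaced, her event kept: 1/16 gives 26.4%; 2/16 gives 34.4%.

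Against the 30% limit in 14.7.2, one event still passes and two still fail. In these cases the decision does not change.

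**The case against.** The best reply is that the power to stop is ample. Section 13.6 permits continuation and does not require it. Item (f) of 13.7.1 applies even to conditions that the management section leaves out. A criterion 3 finding brings the PSRT in, since restarting enrollment needs its unanimous agreement, and item (g) lets it end the woman's dosing. Sections 13.5 and 13.7.2(e) add further routes, and 13.8 requires continuous close monitoring by the investigators. All of this stands. It means that the gap is in the default, not in the authority to stop. It does not remove the gap: the written default for grade 2 is to continue, and every route away from it is the woman's request or a judgment, in Segment B often by staff who cannot reliably be blinded (14.5).

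A reader might infer more than the text supports.

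- *That 13.6 contradicts 13.4.* It does not do so flatly. A specific, mandatory hold can be read as an exception to a general permission, and staff can comply with both. What is missing is a sentence saying so.
- *That promised hold criteria were lost.* Section 13.6 answers by deciding against holds by grade. The sentence in 13.1 is a stale pointer.
- *That a written rule would prevent different handling of the two arms.* It would narrow discretion, but recognizing and measuring the lesion would remain a clinical judgment.
- *That bleeding of other kinds needs its own mandatory exam.* The ad hoc visits, the telephone call and clinical follow-up already cover it. A new rule would rest on the same reporting and judgment.

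**Conclusion.** The point holds and should be fixed. The protocol names one grade 2 finding, and one finding without a grade, as reasons to pause or stop enrollment, yet sets no automatic stop of film for the woman concerned. At the Day 1 exam this leaves up to 6 of 7 planned films (7 of 8 with a Day 8 visit) subject to discretion alone. That count assumes the finding is made at that visit and that nobody uses the discretionary routes. The protocol gives no human rate for these lesions, so no expected number of affected women can be stated. The overlap of 13.4 with 13.6 and the pointer in 13.1 are lesser matters of drafting. Neither the gap nor its repair alters the 30% criterion in the cases worked above.

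**What to change.** - **13.7.1**: add *a finding meeting 13.8 criterion 2 or 3, whatever its grade: stop film permanently for that woman and report to the PSRT*.
- **13.6**: add *except as specified in 13.4 and 13.7.1* to the sentence on Grade 1 and 2 events.
- **13.1**: point to 13.4, 13.6 and 13.7.1 in place of the general reference to hold criteria.

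The cost is a short amendment to three sections. A woman stopped under the new item may become non-evaluable and be replaced. The plan enrolls about 43 for 38 evaluable, so about 43 − 38 = 5 extra enrollments are already foreseen, though ordinary loss to follow-up draws on the same margin. The evaluable target does not change, her adverse event stays in the primary analysis under 14.2, and she is still followed with her permission under 13.7.1.

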### **13.7 CRITERIA FOR DISCONTINUATION**

#### **13.7.1 Permanent Intervention Discontinuation,**

The criteria for permanent discontinuation of further study product(s)/ intervention(s) for an individual participant are:

- a) Grade 3 or 4 Adverse Event (per Section [13.6](#))
- b) Requirement for prohibited concomitant medications
- c) Pregnancy
- d) Completion of study product course as defined in the protocol
- e) Request by participant to terminate study product
- f) Clinical conditions, which in the best judgment of the investigator, are believed to be harmful or potentially life-threatening to the participant, even if not addressed in the AE Management section of the protocol
- g) Recommended by the EC/IRB, PSRT, DAIDS Medical Officer, OHRP, or FDA

The participant will continue to be followed with her permission if study product is discontinued. No subsequent modifications to the visit schedule and duration of continued follow-up will be made, except for discontinuation of the study product.

### **13.7.2 Permanent Study Discontinuation,**

The criteria for premature discontinuation from the study for an individual participant are:

- a) Lost to follow up as evidenced by failure by the participant to attend 2 consecutive clinic visits, at the discretion of the site investigator
- b) Participant repeatedly non-compliant (has not inserted any home doses of film by day 4 when contacted by telephone safety call)
- c) Pregnancy or breastfeeding (if applicable)
- d) Request by participant to withdraw[SEP]
- e) Has any other condition that, in the opinion of the Investigator or designee, would preclude informed consent, make study participation unsafe, complicate interpretation of study outcome data, or otherwise interfere with achieving study objectives.

## **13.8 SAFETY MONITORING**

The study site investigators are responsible for continuous close safety monitoring of all study participants, and for alerting the Protocol Team and IRB if unexpected concerns arise. A sub-group of the Protocol Team, including the Protocol Chair or designee, the DAIDS Medical Officer, and an IPCP Co-PI will serve as the Protocol Safety Review Team (PSRT). If necessary, external experts representing expertise in the fields of microbicides, biostatistics, HIV transmission, and medical ethics may be invited to review the events. The PSRT and the study site will cooperate closely to monitor participant safety and respond to occurrences of toxicity in a timely manner. Study staff will seek to maintain close and effective communication with study participants and communication with and cooperation among study staff, investigators, the PSRT, and the DAIDS Medical Officer. The following findings will serve as the minimum criteria to pause or stop enrollment in Segment A, prevent the initiation of Segment B, and pause or stop enrollment in Segment B. However DAIDS and/or the PSRT can stop the study at any time for any concerning findings of lesser severity than those listed here:

1. If any participant manifests a grade 3 or higher AE that is judged to be related to study product
2. If any participant develops deep epithelial disruption or ulceration of the genital epithelium.
3. If any participant develops erythema or edema of more than 50% of the combined vaginal and cervical surface (grade 2) or more than 50% of the vulvar surface (grade 2).

If enrollment is paused, its reinstitution will require the unanimous agreement of all members of the PSRT.

### **13.9 CLINICAL DATA SAFETY REVIEW**

The Data Management Team will generate data summaries on a monthly basis for the PSRT. These data summaries will include adverse event, accrual and retention data. The Protocol Chair (or designee) will evaluate adverse event data independently and present those to the PSRT on the monthly calls, and present adverse event data to the PSRT via telephone for review. If more urgent safety matters arise, these calls can occur more frequently. The PSRT will determine whether or not the study protocol should continue as originally designed, should be changed, or should be terminated.

The IRB will be notified of any serious and unexpected adverse events according to the policies outlined in the Miriam Hospital IRB Policy and Manual of Operations.

The following information will be submitted to the Miriam Hospital, and Boston University Medical Center IRB at the time of renewal of a research protocol, as required by IRB guidelines:

- The frequency of monitoring during the renewal interval, including the dates of data and safety monitoring;
- A summary of any assessment performed to evaluate external factors or other relevant information that may have an impact on the safety of study participants or the ethics of the research study;
- A summary of the outcome of procedural reviews conducted to ensure subject privacy and research data confidentiality;
- Any conclusions regarding changes to the anticipated benefit-to-risk ratio of study participation and final recommendations related to continuing, changing, or terminating the study, with accompanying rationales as appropriate.

## **14. STATISTICAL METHODS**

### **14.1 REVIEW OF STUDY DESIGN**

The primary aim of this study is to assess the local and systemic safety of MB66, a vaginal anti-microbial consisting of two monoclonal antibodies (MAbs) formulated in a polyvinyl alcohol film. One of the MAbs in MB66 neutralizes herpes simplex virus type 2 (HSV-2), and the other neutralizes human immunodeficiency virus, type 1 (HIV-1). The first segment of the study is a single dose study of MB66 film administered to the vagina in adult healthy female study participants. The second segment of the study is a repeated dose study with seven daily vaginal administrations of MB66 film or placebo film in adult healthy female participants.

Screening for sexually transmitted infections (HIV, *C. trachomatis*, *N. gonorrhoeae*, *T. vaginalis*, *syphilis*, *mucopurulent cervicitis* and *active genital ulcers*), pregnancy, and a routine pelvic exam will be conducted at Visit 1, and urogenital, systemic and menstrual symptoms will be collected via symptom review with participants to exclude study candidates with pre-existent

reproductive tract inflammation and epithelial disruption. This testing will be repeated during subsequent examinations if clinically indicated. Data on epithelial inflammation and disruption will be collected during visual examination of the reproductive tract. Pharmacokinetic measures will assess the rate of film dissolution and the local concentrations of and systemic absorption of MB66 MABs following a single and a seven-day exposure. Assessments of immune mediator concentration and various measures of vaginal ecology will be made before and after MB66 film use.

